#### *Covariates and effect modifiers*

Group-level covariates considered for the analysis include site (KPNW and OHSU), insurance type, inpatient care unit, smoking cessation program used, and medications used. Individual-level covariates include age, sex, ethnicity and race, marital status, amount smoked per day, time to first cigarette, stage of readiness, depression screen positive, alcohol abuse screen positive, socioeconomic status (income, education), and other smokers in the household. Though power will be limited, we will report treatment effects for race/ethnicity categories and by sex.

Secondary analyses will use self-reported seven-day and continuous abstinence at six and twelve months, biochemically confirmed seven-day abstinence at six months, number of quit attempts during the prior year (modeled as Poisson), and amount smoked among continuing smokers (modeled as Poisson).

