### Study interventions

At each hospital, the patient’s tobacco-use history is assessed at bedside by an admitting nurse and recorded in the EMR. A TTS at each hospital reviews the EMR for initial study eligibility (prescreening) prior to conducting a bedside consult and screening visit. All study participants receive a brief (10-minute) bedside tobacco-use evaluation and cessation consult that serves as the usual care condition. All intervention service and medication use, both as an inpatient and after discharge, will be tracked for all study participants. Internal evaluation data indicate the use of outpatient cessation services and medications following hospital discharge was extremely rare (<1% of discharged smokers) among KPNW and OHSU members.

We expect that about 15% of UC recipients will be smoke-free at six months. Unpublished evaluation data for hospitalized KPNW members and OHSU consult recipients suggest about 15% of discharged patients will remain abstinent six months after discharge. Stevens *et al*. (2000) [10] reported a 14.6% quit rate for KPNW hospitalized smokers receiving an intervention similar to our usual care. We estimate that 23% of AR + IVR recipients will be abstinent at six months, given an odds ratio of 1.65, compared to UC recipients [3].

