#### *Inpatient tobacco cessation consult (usual care)*

The usual care (UC) intervention provided by the TTS involves a tobacco-use and quit history assessment, discussion of the health consequences of tobacco use and benefits of quitting, and tailored discharge treatment recommendations based on the patient’s tobacco history and personal circumstances. Tobacco-use assessment includes the types of tobacco used, amount used per day, age at initiation, and use by other family members. Quit history includes the number of past quit attempts made, how long ago they last tried to quit, and their experience with using cessation programs and medications. If they used medications, patients are asked about the types of medications used (nicotine replacement therapy [NRT], bupropion, varenicline), how they liked it, and if they experienced any side effects. If appropriate, a tailored discussion is provided of the relationship between tobacco exposure and the patient’s diagnosis, and the health benefits from remaining abstinent. Patients are encouraged to remain abstinent after discharge and provided printed information about available outpatient resources.

UC recipients are provided printed information and a brief overview of existing counseling programs and FDA-approved cessation medications that are typically covered by the patient’s health insurance. UC patients are informed about how to access available services on their own, that is, the TTS does not actively assist the patient in enrolling in a program or ordering medications.

At KPNW, patients access outpatient cessation services and medications through the Health Education Services (HES) department. Patients can enroll in telephone-based and in-person counseling programs, or an interactive web-based program, by contacting HES on their own. Available medications include over-the-counter NRT (transdermal patch, gum, lozenges) and prescription bupropion and varenicline. KPNW patients are charged a small copayment for the services they select, and must enroll in an approved counseling program in order to receive medications at copay. Patients can purchase cessation medications at discharge, typically through the patient’s attending physician; however, the patient will be required to enroll in a counseling program through HES in order to get medications at copay.

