#### *AR + IVR Intervention*

AR + IVR assigned patients are assessed for interest and willingness to enroll in stop-smoking services following discharge. Those who express interest are helped to enroll in available programs before leaving the hospital and staff initiate discharge orders for cessation medications. At KPNW, available programs include alternative telephone counseling programs, individual and group classes, and an interactive web-based program. All programs, except the web-based program, have been shown to be effective at helping smokers quit [9,15,18]. KPNW currently offers nicotine replacement therapy (transdermal patches, lozenges, gum), bupropion, and varenicline. OHSU participants will be offered enrollment in the Oregon Tobacco Quit Line (OTQL) and provided information about available resources and medication options. Information about study enrollment and recommended options for postdischarge cessation treatment will be sent to each patient’s primary source of health care via internal EMR notes or external fax or electronic notes. At both sites, the out-of-pocket costs for enrolled services are determined by participants’ insurance coverage.

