#### *IVR follow-up calls*

After discharge, AR + IVR recipients receive four IVR follow-up calls, at days 4, 14, 28, and 49 using Eliza Corporation’s IVR system [19]. The call receipt window will be +4 days for the initial call, and ±4 days for each subsequent call. Participants are prompted for information on current smoking status, cessation program enrollment status, and assessment of cessation medication use. Patients also receive brief, tailored, supportive messages to help them stay off cigarettes. These messages include encouragement to enroll in cessation programs, use cessation medications, or to speak to their doctor to determine the best course of treatment. IVR alerts are generated when a patient indicates that he/she would like to speak to an OTQL quit coach or KP health coach during the call. Study staff members facilitate a callback from the respective coach.

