Model 1 specifies only one source of systematic variation among the trial conditions, C_k_. Any factor other than the intervention that favors one condition over the other serves to bias the estimate of the intervention effect. Since this is a randomized trial, there are no differences expected between treatment and control arms in the distribution of covariates. However, there might be unmeasured factors at the various sites that might result in varying effect sizes between the two arms. These factors are potentially confounded with site. In the adjusted analysis, site, interaction between site and treatment, and measured covariates are added to the analysis to reduce confounding and to improve the precision of the estimate of the intervention effect. Covariates can be measured at the site or patient level. Covariates measured at the group (site) level and patient level are distinguished as **G** and **M**. With covariates at two levels and patients nested within sites, we shift to a two-level generalized linear model with logit link. Level 1 involves patient-level variables: $\text{logit}\;\left[Y_{\text{ick}}\right]=\beta_{0c}+\beta_{1c}X_{k}+\beta_{2c}M_{i}+e_{\text{ick}}$, where **M**_i_ is a vector of patient-level covariates (bold indicates a vector throughout this section), *β*_0c,_*β*_1c_, and ***β***_2c_ are patient-level parameters that are allowed to vary over sites, and c = 1, . . ., C clinical sites, and e_ick_ is the residual.

The level-1 model implies three level-2 equations to model variation between sites in patient-level parameters and adds the effect of site-level covariates:

where γ_0._, γ_1_., γ_2_ are parameters to be estimated, Sc is the vector of c-1 site indicators, Gc is the vector of site-level covariates, and u are residual terms. The resulting combined two-level model is of the form:

(1)$$\text{logit}\;\left[Y_{\text{ick}}\right]={ϒ}_{00}+{ϒ}_{01}Sc+{ϒ}_{02}Gc+u_{0c}+\left[{ϒ}_{10},+,{ϒ}_{11},S,c,+,{ϒ}_{12},G,c,+,u_{1c}\right]X_{k}+\left[{ϒ}_{20},+,{ϒ}_{21},S,c,+,{ϒ}_{22},G,c,+,u_{2c}\right]M_{i}+e_{\text{ick}},$$

that simplifies to (Model 2):

(2)$$\text{logit}\left[Y_{\text{ick}}\right]={ϒ}_{00}+{ϒ}_{01}Sc+{ϒ}_{02}Gc+\left[{ϒ}_{10}+u_{1c}\right]X_{k}+{ϒ}_{11}S{\text{cX}}_{k}+{ϒ}_{12}G{\text{cX}}_{k}+\left[{ϒ}_{20}+u_{2c}\right]M_{i}+{ϒ}_{21}ScM_{i}+{ϒ}_{22}GcM_{i}+u_{0c}+e_{\text{ick}},$$

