#### *Specific Aim 2: estimate the dose effect on smoking abstinence at six and twelve months for the AR + IVR compared to usual care*

Variation in outpatient service use is used to assess a dose–response effect for cessation services. We test the hypothesis in two ways using the model developed for Specific Aim 1. First, we will include only AR + IVR recipients and redefine X as a multilevel ordinal variable representing intervention dose (D_r_) ranging from no postdischarge intervention to full intervention. The number of levels to D_r_ will be determined using a rank scoring algorithm that includes cessation service program enrollment and completion, cessation medications, and number of IVR follow-up calls received. Additional inputs will be considered based on actual study data. Second, we will rerun the analysis including control group participants with a dose score using the same method. For each analysis, we will conduct trend tests and assess the presence of a dose threshold.

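### The adjusted Aim 1 model lists cessation program use and medication use as candidate covariates; if included, they take the mediated part of the effect out of the adjusted estimate

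*Protocol article*

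**What the plan says.** Under Specific Aim 1, the treatment effect on thirty-day abstinence is first tested in Model 1, a logistic regression with treatment as the only term, by a score chi-square test. An adjusted analysis (Model 2) follows, in which "site, interaction between site and treatment, and measured covariates are added to the analysis to reduce confounding and to improve the precision" of the treatment estimate. Model 2 separates site-level covariates (G) from patient-level covariates (M) and contains G-by-treatment terms.

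The section Covariates and effect modifiers supplies the list: "Group-level covariates considered for the analysis include site (KPNW and OHSU), insurance type, inpatient care unit, smoking cessation program used, and medications used". The individual-level list that follows contains demographic, smoking-history and screening variables.

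On the two variables at issue, the article also says:

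- **AR + IVR Intervention:** "Those who express interest are helped to enroll in available programs before leaving the hospital and staff initiate discharge orders for cessation medications".
- **IVR follow-up calls:** "These messages include encouragement to enroll in cessation programs, use cessation medications, or to speak to their doctor".
- **Usual care:** "the TTS does not actively assist the patient in enrolling in a program or ordering medications".
- **Study interventions:** on internal data, "the use of outpatient cessation services and medications following hospital discharge was extremely rare (<1% of discharged smokers".
- **Intervention dose:** counseling and medication are recorded from the inpatient consult to twelve months, to assess fidelity and dose response.
- **Specific Aim 2:** the dose score is built from program enrollment and completion, medications and IVR calls received. "We test the hypothesis in two ways using the model developed for Specific Aim 1".

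**The concern.** A covariate can confound a randomized comparison, or safely sharpen it, only if assignment does not alter it. Program enrollment and medication use are what assisted referral is meant to raise, and they are expected in turn to raise abstinence. Conditioning on them asks how the arms compare among patients with the same treatment uptake. That is not the effect of offering AR + IVR.

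Two things follow if they are included. First, the part of the effect that runs through uptake leaves the treatment coefficient. Second, uptake is self-selected, so conditioning on it can induce an association between arm and unmeasured causes of quitting. A user in UC, who had to enroll unaided, is likely to be more motivated than a user in AR + IVR.

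Model 2 adds a further difficulty. Both variables are labelled group-level although use varies by patient, and group-level covariates are crossed with treatment. The treatment main effect would then be the effect at a reference level of use. At stake is a planned adjusted result on the primary outcome, which could look null beside a positive unadjusted one.

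**Working it through.** **1. Are these post-randomization variables?** Past program and medication experience is taken at the bedside consult, so past use is a possible meaning. Four points favor in-study use:

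- The covariate list does not say past.
- The baseline variables named under Other patient information for the outcome analyses include neither item.
- The text after Model 2 makes its moderator interpretation conditional on baseline measurement, which implies that some covariates are not baseline.
- Intervention dose and Specific Aim 2 use the same terms for treatment during the study.

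**2. The plan's own figure.** Inputs from the Power section: p0 = 0.15 (UC), p1 = 0.23 (AR + IVR), two-sided α = 0.05, power 80%, allocation k = 2, no continuity correction.

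n(UC) = [1.960·√(1.5·p̄(1−p̄)) + 0.842·√(p0(1−p0) + p1(1−p1)/2)]² / (p1−p0)², with p̄ = (0.15 + 2×0.23)/3 = 0.2033.

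= [0.966 + 0.391]² / 0.0064 = 287.9, so 288 UC + 576 AR + IVR = 864. The stated figure reproduces. Power at 300:600 is 81.7%. The implied odds ratio is (0.23/0.77)/(0.15/0.85) = 1.69.

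**3. Effect of conditioning on use.** Let s be the share of the 8-point difference that runs through use, and u0 and u1 the use rates in UC and AR + IVR. The article gives none of these for the trial, so they are assumptions. The marginal rates stay at 15% and 23%:

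- risk difference from use: g = 0.08·s/(u1−u0)
- UC non-users: q = 0.15 − g·u0; UC users: q + g
- AR + IVR: add the direct part, 0.08·(1−s), in both strata

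Worked case, s = 0.5, u0 = 0.10, u1 = 0.50: g = 0.04/0.40 = 0.10 and q = 0.15 − 0.01 = 0.14.

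| | Non-users | Users |
|---|---|---|
| UC | 0.14 | 0.24 |
| AR + IVR | 0.18 | 0.28 |

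Check: 0.9×0.14 + 0.1×0.24 = 0.15, and 0.5×0.18 + 0.5×0.28 = 0.23. The stratum odds ratios are 1.35 (non-users) and 1.23 (users). The fitted common odds ratio is 1.32, against 1.69 unadjusted.

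Logistic regression on expected data, 300 UC and 600 AR + IVR, treatment plus a binary use covariate, over u0 of 1–20% and u1 of 20–70%:

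| Share through use | Adjusted OR | Wald power for treatment |
|---|---|---|
| no use covariate (Model 1) | 1.69 | about 80% |
| 25% | 1.50–1.51 | 39–55% |
| 50% | 1.32–1.33 | 21–30% |
| 75% | about 1.16 | 9–12% |
| 100% | 1.00 | 5% |

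**4. Common causes.** The table contains no shared cause of use and quitting. As an illustration only, a simulation with full mediation and an unmeasured factor acting at 0.7 log-odds per SD on both use and quitting takes a total odds ratio of about 1.6–1.8 to an adjusted one of about 0.85. That factor and its strength are invented, so the result shows the direction of this bias and not its likely size.

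The fits in steps 3 and 4 have no use-by-treatment term. With one, the reported main effect would be a stratum effect at the chosen reference level, such as the 1.35 or 1.23 of the worked case.

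**The case against.** The strongest reply is that the main test is untouched. Model 1 contains treatment only, and all randomized patients are to enter the intention-to-treat analysis of the primary outcome. A reader might infer that the adjustment removes the effect under test or that the trial's primary result is compromised. The article does not support this: Model 2 is an additional, adjusted analysis. This part of the objection stands in full.

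Three further points stand in part.

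- **Inclusion is not certain.** The covariates are only under consideration, in a condensed article. The consequences are therefore conditional on inclusion. Even so, nothing in the text limits the list to baseline variables.
- **The meaning is not settled.** Past use is recorded, and a group-level label fits individual in-study use poorly. The article's other uses of the terms make in-study use the likelier reading, but the remedy should allow for clarification.
- **Full removal is the extreme case.** AR + IVR patients also receive four calls with tailored supportive messages, a plausible path that needs neither program nor medication. An adjusted odds ratio of 1.00 follows only if the whole effect runs through use; otherwise the result is attenuation.

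A reader might also infer that Aim 2 certainly adjusts dose for its own components. The article says the Aim 1 model is reused with the treatment term redefined. It does not say that the two covariates are kept.

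**Conclusion.** The point holds for the adjusted Aim 1 analysis. As the article uses these terms elsewhere, program used and medications used describe post-randomization uptake that AR + IVR is built to increase. Including them would not reduce confounding. It would take the mediated part out of the adjusted estimate and could add bias from self-selection.

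At the planned rates, the adjusted odds ratio falls from 1.69 to about 1.50, 1.32, 1.16 or 1.00 as the mediated share rises through 25%, 50%, 75% and 100%. The result depends mainly on the mediated share and hardly at all on the use rates tried. An adjusted null beside a positive Model 1 could thus be an artefact.

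If the same covariates are carried into Aim 2, the dose score would be adjusted for its own components. The Model 1 test, the 864 and the 900 stand.

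**What to change.** - Delete program used and medications used from the Model 2 covariates and effect modifiers. If past use was meant, say that only use before admission counts.
- State that Model 2 is restricted to variables fixed before randomization. Keep every baseline covariate already listed: site, insurance type, care unit and the whole individual-level list, including race/ethnicity, marital status and stage of readiness.
- Use in-study program and medication use only in the Aim 2 dose analysis or in a separately labelled mediation analysis, and state that they are not also covariates there.

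The cost is a sentence or two in the analysis plan. No data collection, sample size or patient contact changes.

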#### *Power*

A 2:1 ratio of AR + IVR to UC for 900 randomized participants will provide adequate power to detect an eight percentage point difference in thirty-day point prevalence abstinence at six months (our primary outcome), assuming an unbiased method of assigning an outcome to nonrespondents. The unbalanced design requires 864 participants to achieve 80% power, with two-tailed α set at .05, to detect a difference in thirty-day abstinence of eight percentage points between treatment groups. We expect the UC group will achieve a 15% abstinence rate, based on analyses of EMR data (unpublished) for similar populations at each site. An odds ratio of 1.65 for patients with >30 days of follow-up [3] results in a 23% expected abstinence rate for the AR + IVR group. The power calculations were conservative [25-28] and no continuity correction was applied. Rounding up to 900 total participants added an additional measure of conservatism.

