#### *Additional tobacco measures*

For participants reporting having smoked during the follow-up period, we assess amount smoked per day, and the first two consecutive days smoked postdischarge, to calculate relapse curves by group assignment. We also collect baseline and follow-up information about other tobacco use, including cigars, pipes, bidis, hookahs, and smokeless tobacco to control for substitution. We ask about other household smokers and indoor smoking rules.

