#### *Specific Aim 1: estimate self-reported thirty-day abstinence at six and twelve months for patients assigned to receive inpatient AR + IVR compared to usual care*

Based on KPNW and OHSU member data and meta-analyses of effectiveness of hospital cessation programs with ≥1 month postdischarge follow-up, we expect about 15% of usual care patients and 23% of AR + IVR participants will be abstinent six months following discharge. The primary analysis assumes that nonrespondents are smokers.

The treatment effect on the primary outcome (and other binary outcomes) will be evaluated using logistic regression, logit[Y_ik_] = β_0_ + β_1_X_k_ + e _ik_ (Model 1), where Y_ik_ is the binary indicator of the observed binary smoking status for the i^th^ patient (i = 1,. . .,n_k_) within the k^th^ treatment condition (k = 1,2), X_k_ is the fixed effect of the k^th^ condition, that is, intervention or control, and β_0_, β_1_ are parameters to be estimated. Any difference between the predicted and observed values is left to the residual error (e _ik_) in this model. Multiple regression methods available in SAS PROC Logistic [33] will be used to estimate the parameters of this generalized linear model. The intervention fixed effect will be tested using the score *χ*^2^ test.

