#### *Specific Aim 4: evaluate health care utilization at twelve months for AR + AVR and usual care*

We measure health-care utilization for AR + AVR compared to UC by the mean number of combined outpatient and inpatient encounters (visits) per participant during follow-up. This aim is addressed using participant survey responses and medical records (electronically for those receiving care at KPNW and OHSU facilities). For AR + IVR compared to UC, we measure health-care utilization by the mean number of combined outpatient and inpatient encounters (visits) per participant during follow-up. This aim will be addressed using participant survey responses and medical records (electronically for those receiving care at KPNW and OHSU facilities). The functional form of models 1 and 2 for the primary aim will be restated within a Poisson regression model structure and analyzed using SAS PROC GENMOD, specifying a log link function and Poisson distribution.

Health-care utilization data are regularly characterized by nonnormal distributions. While zero values are not expected for visits in the study population, there may be substantial variation in the number of visits completed. Depending on the number of inpatient visits, analysis of the number of inpatient days separately from outpatient visits may be conducted. If the variance is greater than the mean, we will control for the impact of overdispersion by including a term in the model for the unobserved heterogeneity of each i^th^ observation. If data allow separate modeling of inpatient days, the large number of zero stays will require specifying a zero-inflated negative binomial model.

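### Two secondary counts are assigned Poisson models without the overdispersion handling given to health-care visits, and the amount-smoked contrast is confined to continuing smokers without being labelled non-randomized

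*Protocol article*

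**What the plan says.** The Covariates and effect modifiers section of the protocol article opens its list of secondary analyses with binary outcomes ("Secondary analyses will use self-reported seven-day and continuous abstinence at six and twelve months") and ends it with two counts: "number of quit attempts during the prior year (modeled as Poisson), and amount smoked among continuing smokers (modeled as Poisson". No dispersion parameter, robust variance or alternative distribution is mentioned there.

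Amount smoked is collected only from a subset defined after randomization. Under Additional tobacco measures: "For participants reporting having smoked during the follow-up period, we assess amount smoked per day".

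The article does deal with overdispersion in one place, Specific Aim 4: "If the variance is greater than the mean, we will control for the impact of overdispersion by including a term in the model". It also names a zero-inflated negative binomial model for inpatient days. That paragraph is introduced by "Health-care utilization data are regularly characterized by nonnormal distributions", and nothing carries it over to the two smoking counts.

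**The concern.** A Poisson model sets the variance equal to the mean. If the true variance is larger, the model-based standard error is too small, intervals are too narrow and the test rejects too often. The article recognizes this for visits but not for two other counts, one of which (cigarettes per day) is likely to be widely spread: eligibility runs from a single puff in the past 30 days up to any level of daily smoking, in adults of all ages at two hospitals.

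The second issue concerns amount smoked only. Being a continuing smoker is the complement of the outcome the intervention is meant to change. If lighter smokers quit more readily and AR + IVR produces more quitters, the remaining AR + IVR smokers will be somewhat heavier on average even if nobody's consumption was affected.

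At stake are the p-values and intervals of two secondary analyses, and how the amount-smoked contrast is read.

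**Working it through.** **Plan's own figure first.** The Power section states: "The unbalanced design requires 864 participants to achieve 80% power, with two-tailed α set at .05". With 15% v 23%, 2:1 allocation, pooled variance under the null and no continuity correction, p̄ = (0.15 + 2 × 0.23)/3 = 0.2033 and

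n(UC) = [1.96 √(1.5 × 0.2033 × 0.7967) + 0.8416 √(0.15 × 0.85 + 0.23 × 0.77/2)]² / 0.08² = 287.9, so 288 + 576 = 864.

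This reproduces exactly. It concerns the binary primary outcome; no sample-size figure is given for the counts.

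**Overdispersion.** Let φ = SD²/mean. The true standard error is √φ times the Poisson one, and the actual size of a nominal 5% test is 2[1 − Φ(1.96/√φ)]. Poisson would require an SD of √10 = 3.2 at a mean of 10, or √15 = 3.9 at a mean of 15. All means and SDs below are assumptions.

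| Outcome | Mean / SD | φ | SE factor | Actual size |
|---|---|---|---|---|
| Cigarettes per day | 12 / 5 | 2.08 | 1.4 | 17% |
| | 10 / 6 | 3.6 | 1.9 | 30% |
| | 15 / 9 | 5.4 | 2.3 | 40% |
| | 15 / 10 | 6.67 | 2.6 | 45% |
| Quit attempts | 2 / 1.41 | 1.0 | 1.0 | 5% |
| | 2 / 2 | 2.0 | 1.4 | 17% |
| | 2 / 3 | 4.5 | 2.1 | 36% |
| | 3 / 4 | 5.33 | 2.3 | 40% |
| | 3 / 6 | 12.0 | 3.5 | 57% |

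The cigarette rows do not exhaust means of 10 to 15 and SDs of 5 to 10. The corners give 1.3 times and 13% (15/5), and 3.2 times and 54% (10/10).

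Negative binomial simulation under no effect (2,000 runs) agrees with the formula. For cigarettes at 10/6, 10/8 and 15/10, with 255 v 462 smokers, the plain Poisson test rejected 30%, 45% and 44%. For quit attempts at 2/2, 2/3 and 3/4, with 300 v 600, it rejected 16%, 36% and 40%. With robust or scaled standard errors, every case came back to about 5% to 6%.

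Adjustment for baseline consumption reduces φ. In a simulation with assumed lognormal consumption it fell from about 10 to about 3. At φ = 3 the factor is √3 = 1.7 and the size is 2[1 − Φ(1.96/1.73)] = 26%: smaller, but not 5%.

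**Selection into the amount-smoked comparison.** Specific Aim 1 states: "we expect about 15% of usual care patients and 23% of AR + IVR participants will be abstinent six months following discharge". The comparison therefore keeps 300 × 0.85 = 255 UC and 600 × 0.77 = 462 AR + IVR participants. If 85% are followed and all expected abstainers are among them, amount smoked is observed in 300 × 0.85 − 45 = 210 and 600 × 0.85 − 138 = 372.

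Take lognormal consumption (median 11, log SD 0.6), no effect on anyone's consumption, and log-odds of quitting falling by 0.3, 0.5, 0.8 or 1.0 per SD of log consumption (all assumed). The AR + IVR to UC ratio of mean cigarettes is then 1.013, 1.021, 1.030 or 1.034. A separate simulation of the same mechanism gave 1% to 4% unadjusted, and −0.1% to +0.2% after adjustment for baseline consumption. A shift of about 1.1 cigarettes per day (15.60 v 16.69, or 7%) appeared only when a stronger intervention effect in light smokers was added.

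**The two together.** At mean 15, the Poisson standard error of the log ratio is √[1/(255 × 15) + 1/(462 × 15)] = 0.020. A 1% to 3% selection shift is thus about 0.5 to 1.5 Poisson standard errors, so a small artefact looks larger than it should when the standard error is understated.

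**The case against.** The strongest reply is that a parenthesis in a condensed journal article names a distribution and does not commit anyone to unscaled standard errors. Where the article writes a Poisson model out, it plans to check dispersion, and scale or robust options for minor counts are often left to the full protocol or SAP. This stands in part: it cannot be said that the trial will certainly use uncorrected errors. But a model is stated for these two outcomes, and the overdispersion provision is written for health-care utilization alone. Followed as written, the text gives Poisson standard errors.

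Four stronger readings are tempting and are not supported:

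- **Standard errors far too small for both counts.** No mean, SD or dispersion is given for either. The case is strong for cigarettes per day, where the eligibility range makes an SD of 3 to 4 implausible. For quit attempts it depends wholly on unstated dispersion and may be nil.
- **Both comparisons non-randomized.** Only amount smoked is restricted to continuing smokers. The restriction is stated openly, and the article nowhere presents the contrast as a randomized effect on consumption.
- **A serious selection bias.** The likely shift is 1% to 4%. Amount smoked per day is already a listed covariate, and its baseline value largely removes the shift when selection acts through baseline consumption. The adjusted count model is not written out, however.
- **Abstainers must be scored as zero.** That asks a different question, mixing quitting with reduction. It adds some 15% to 23% zeros that a simple negative binomial may not fit, and it needs a rule for nonrespondents.

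It is also fair that neither count appears among the additional outcomes in the abstract or the outcomes described under Primary outcome. They appear only as secondary analyses.

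**Conclusion.** The point holds in limited form. The article specifies Poisson for quit attempts and for amount smoked among continuing smokers without the overdispersion handling it gives to visits. For cigarettes per day the standard error would very likely be understated, by about 1.4 to 2.6 times under the tabulated assumptions, with a nominal 5% test rejecting about 17% to 45% under the null and less after baseline adjustment. For quit attempts the understatement runs from none to large. The amount-smoked contrast alone conditions on a post-randomization outcome; its bias is probably small, about 1% to 4% unadjusted.

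All these sizes rest on assumed distributions. A reader might infer that the main result is at risk. It is not: the primary outcome, its logistic analysis and N = 864 do not depend on either count. The change is worth making because it alters the intervals and p-values of two stated secondary analyses at almost no cost.

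**What to change.** In Covariates and effect modifiers:

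1. Specify negative binomial regression, or Poisson with robust or scale-adjusted standard errors, for both number of quit attempts and amount smoked, from the outset and not conditional on a dispersion check.
2. State that the amount-smoked model adjusts for baseline cigarettes per day.
3. Label the comparison among continuing smokers descriptive and non-randomized.

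An analysis of all participants with abstainers at zero may be added as an optional extra, described as answering a different question and with a stated rule for nonrespondents.

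The cost is a model option in PROC GENMOD, which the article already names for Aim 4, and a few sentences. No new data are needed. Intervals will be somewhat wider where overdispersion is present and essentially unchanged where it is not.
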